### Statistical analysis

2.9

Statistical analyses will be performed using the principle of the full analysis set (FAS). For the intention-to-treat analysis, missing values will be analyzed as last observation carried forward. The baseline values before treatment and the changes in BCSS scores after 4 weeks of treatment will be measured for the experimental and control groups. To test the mean rank sum of BCSS changes after the 4 weeks compared to baseline between the 2 groups, the Mann–Whitney-Wilcoxon rank sum test will be performed. The treatment difference between the treatment and control groups will be estimated using the Hodges-Lehmann method, and a 95% nonparametric confidence interval will be presented. The confidence level will be set to 5%. All statistical analyses will be performed using SPSS Statistics for Windows version 21.0 (IBM Corp., Armonk, NY).

Descriptive statistics, such as the number of participants, and the mean, standard deviation, minimum, median, and maximum of data, will be presented for each visit, as well as changes from baseline at the final evaluation for continuous data, clinical laboratory tests, and vital signs. No intermediate analyses will be performed.

Descriptive statistics for demographic data and clinical history data for the FAS group will be presented. Continuous data will be tested using *t*-tests or Wilcoxon's rank sum tests. Categorical data will be analyzed using the chi-square test or Fisher exact test.

The safety assessment calculates the rate of adverse events. Continuous data such as comparisons between groups, individual laboratory test results, and biomarkers will be analyzed using paired *t*-tests or *t*-tests with 95% confidence intervals within the group to determine if there are any changes compared to the baseline. If the assumption of normality is not met, nonparametric statistical analyses (Wilcoxon signed rank test or Wilcoxon rank sum test) will be performed. Categorical data will provide frequencies and ratios for each category. The differences between groups will be analyzed using the chi-square test and Fisher's exact test.

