### Sample size calculation

2.4

This study is a pilot trial to explore the effect of LP on the primary and secondary outcome measures selected for a minimum sample size, and to investigate the sample size calculation basis and feasibility for future clinical trials. According to Whitehead et al,^[10]^ when the power is considered to be 80% and effect size is considered moderate, in a preliminary parallel-designed study the empirically optimal sample size is 10 persons per group. As this current study plan includes 2 visits within 4 weeks, high compliance is expected, which suggests a calculated dropout rate of 5%. Therefore, we designed a pilot study involving 22 participants.

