### Outcome measures

2.7

The primary outcome is the BCSS score, which will be used to assess respiratory symptoms, such as dyspnea, cough, and sputum. The secondary outcomes are the pulmonary function test (FVC, FEV1, FEV1/FVC), the clinical symptoms of cough and sputum (assessed through a questionnaire), high-sensitivity C-reactive protein level, erythrocyte sedimentation rate, white blood cell count, eosinophil, T cell, B cell, and immune factors (interleukin (IL)-1β, IL-4, tumor necrosis factor (TNF)-α, IL-6, IL-8, interferon (IFN)-γ, immunoglobulin (Ig)E) to analyze allergic inflammation in the bronchi, antioxidants (glutathione peroxidase, superoxide dismutase, nitric oxide) to analyze bronchial peroxide expression levels, and COPD assessment test score. All outcome measures will be assessed at the first and second visits. To ensure the safety of the participant, we will conduct laboratory tests, such as liver function, complete blood count, and electrolytes, and evaluate vital signs at every visit. Safety assessments will be conducted during the second visit. The participants’ data will be anonymized and coded using a specific program (Fig. 2).

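### The primary analysis of BCSS change makes no adjustment for baseline BCSS: valid, but it gives up precision and exposes the estimate to chance imbalance in a 22-person trial

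*Protocol article*

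**What the plan says.** - **Endpoint.** Section 2.7 (Outcome measures): "The primary outcome is the BCSS score".
- **Baseline is available.** The same section: "All outcome measures will be assessed at the first and second visits". Table 1 agrees, with effectiveness variables measured at Visit 1 (baseline) and Visit 2.
- **Primary test.** Section 2.9 (Statistical analysis) gives the aim as follows: "To test the mean rank sum of BCSS changes after the 4 weeks compared to baseline between the 2 groups". For that purpose it names one method and no alternative: "the Mann–Whitney-Wilcoxon rank sum test will be performed".
- **Primary estimate.** The treatment difference "will be estimated using the Hodges-Lehmann method, and a 95% nonparametric confidence interval will be presented". No covariate is named for the test or the estimate.
- **Allocation.** Section 2.5 describes 1:1 block randomization and states no stratification by baseline score.
- **Size and purpose.** Section 2.4 calls the study a pilot that is to supply the basis for later sample size calculations. It takes as its starting point that "the empirically optimal sample size is 10 persons per group" and arrives at 22 participants.

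The test, the estimator and the interval are all fixed in the article, so this is a stated choice and not a detail left to an analysis plan.

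**The concern.** Subtracting baseline amounts to assuming that each extra point at baseline predicts exactly one extra point at week 4. Symptom scores usually regress towards the mean, so the true slope tends to be below 1 and high scorers tend to fall more. There are two consequences. The change score keeps baseline noise that a fitted slope would remove, so the interval is wider than it need be. And if one arm happens to start higher, part of its larger fall is credited to treatment. With 11 per arm and no stratification by score, such imbalance is not rare. What the reader of a pilot mainly receives is the estimate and its interval, and both are affected.

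**Working it through.** **Inputs from the protocol.** 10 per group before dropout, 5% dropout, 22 in total (section 2.4); 1:1 allocation (2.5); level 5% (2.9), taken as two-sided.

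**Assumptions.** The protocol gives neither rho nor a BCSS standard deviation. I take rho = 0.3, 0.5, 0.7 and 0.9, equal variances s² at both visits, and all 22 participants analysed.

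**The plan's own figure.** 10 / 0.95 = 10.53, rounded up to 11 per group; 2 × 11 = 22. It reproduces.

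**Variance ratio.**
1. Per-person variance of change: 2s²(1 − rho).
2. Per-person residual variance after adjustment for baseline: s²(1 − rho²).
3. Large-sample ratio, adjusted to change: (1 − rho²) / [2(1 − rho)] = (1 + rho)/2.
4. Cost of estimating the slope at N = 22: 1 + 1/(N − 4) = 1 + 1/18 = 1.056.
5. Ratio at N = 22: 1.056 × (1 + rho)/2. The comparator is the difference in mean change.

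| rho | (1 + rho)/2 | Ratio at N = 22 | Equivalent N = 22/ratio | Extra participants |
|---|---|---|---|---|
| 0.3 | 0.65 | 0.686 | 32.1 | 46% |
| 0.5 | 0.75 | 0.792 | 27.8 | 26% |
| 0.7 | 0.85 | 0.897 | 24.5 | 11% |
| 0.9 | 0.95 | 1.003 | 21.9 | none |

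Break-even is at rho = 2/1.056 − 1, about 0.89.

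**Chance imbalance.** The difference in baseline means has standard deviation √(2/11) = 0.43 SD. It exceeds 0.5 SD in either direction with probability 2 × P(Z > 0.5/0.426), about 24%. The difference in mean change moves by −(1 − rho) per unit of baseline difference. In simulation the Hodges-Lehmann estimate behaved the same way, moving by about −0.7, −0.5 and −0.3 at rho 0.3, 0.5 and 0.7, while the ANCOVA estimate did not move. At rho 0.5, a 0.5 SD imbalance therefore shifts the reported effect by about 0.5 × 0.5 = 0.25 SD.

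**Simulated power.** Normal data, 11 per arm, true shift 0.8 SD, 4000 runs per setting:

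| rho | Rank-sum on change | t-test on change | ANCOVA | Rank ANCOVA |
|---|---|---|---|---|
| 0.3 | 31% | 34% | 46% | 43% |
| 0.5 | 40% | 43% | 53% | 48% |
| 0.7 | 60% | 64% | 68% | 62% |

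The t-test column separates the effect of adjusting from the effect of leaving ranks. Type I error was 4.3% to 5.6% for all four methods. A further simulation with rounded, bounded scores (assumed mean 5, SD 1.8) gave the same pattern.

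**The case against.** The best defence is that nothing here is invalid. A rank-sum test on change with a Hodges-Lehmann interval is coherent, pre-specified and protected by randomization. That stands. A reader might infer that the planned estimate is biased. It is so only conditionally on an imbalance that has occurred; averaged over randomizations, the planned and adjusted estimates agree.

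Other strong readings that the protocol does not support:
- **Change is worse whenever rho is below 1.** That overlooks the cost of estimating the slope; at N = 22 the variance gain ends near 0.89. With unequal visit variances, the large-sample break-even is a slope of 1, not a correlation of 1. Four weeks between visits in people with persistent symptoms does not rule out a high rho.
- **A third more participants at rho 0.5.** That is 1/0.75, the large-sample figure; at N = 22 it is 1/0.792, about 26%.
- **The whole power gap comes from adjustment.** Part comes from leaving ranks. At rho 0.7 half of the 8-point gap (60% to 64% to 68%) does, and the rank-based adjustment adds only about 2 points.
- **The next trial's sample size will be inflated.** Section 2.9 promises standard deviations at each visit and for change. From these rho can be recovered as (s₀² + s₁² − s_d²)/(2s₀s₁), and an adjusted analysis can be planned.
- **The Hodges-Lehmann estimate is too coarse because BCSS takes whole numbers.** The protocol does not state the scoring or range of the scale, so this cannot be argued from it.
- **Every secondary outcome needs the same linear model.** No calculation here covers the cytokines and other biomarkers, for which section 2.9 has its own nonparametric fallback.

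What remains is that a covariate already measured in every participant is left out of an analysis where it is likely to help.

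**Conclusion.** The point holds as one of efficiency and robustness to chance imbalance, not of validity. For rho between 0.3 and 0.7, adjustment cuts the variance of the treatment estimate by about 31% to 10% at N = 22. For a 0.8 SD shift, power rises by about 8 to 15 points with ANCOVA, or about 2 to 12 with a rank-based version. These sizes rest on an assumed rho, equal visit variances and a roughly linear relation between baseline and Visit 2 scores. The direction of the benefit is secure only for rho below about 0.89. Because this is a pilot, the practical loss is a wider and less stable estimate rather than a wrong conclusion, but the improvement is close to free.

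**What to change.** In section 2.9, make the primary estimate the treatment difference in Visit 2 BCSS from a linear model with treatment and baseline BCSS, reported with its 95% confidence interval. To keep the plan's caution about non-normality, obtain the supporting p-value from a rank-based ANCOVA or a permutation test, and name which one in advance. Retain the rank-sum test and Hodges-Lehmann interval on change as a sensitivity analysis. Settle the change before the allocation code is opened.

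The cost is one degree of freedom and reliance on a roughly linear baseline relation, which should be checked with a plot. No new data, visits or participants are needed, and the analysis of secondary outcomes need not change on this account.

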## Discussion

3

The lungs and respiratory system prevent various diseases by activating the immune system when viruses invade.^[11]^ However, because they are connected to the outside environment, inflammation occurs easily, leading to symptoms.^[12]^ The most common symptoms are cough, sputum, and shortness of breath; exposure to external fine dust, viruses, and other air pollutants is considered a risk factor.^[4]^

Respiratory diseases such as bronchitis, asthma, and COPD are among the most common diseases, and respiratory symptoms are closely related to discomfort in daily life.^[3]^ Therefore, interest in easily accessible health functional products and complementary medicine has increased. Studies are being actively conducted to discover immune-enhancing substances or extracts isolated from natural herbal supplements.^[13]^

As a traditional Asian herbal medicine, LP has long been used for the treatment of asthma, as well as bronchial and lung inflammation,^[14,15]^ and it is said to act as a defense mechanism against fine dust and respiratory diseases.^[16]^

There have been previous studies on the actions and effects of LP. Kim et al reported that LP generated an immunomodulatory effect through T cells and the promotion of INF-γ secretion.^[17]^ Ryu et al reported the effects of LP on the secretion of cytokines, eosinophils, and IgE in relation to asthma.^[16,18]^ Kim et al reported the effects of LP on immune cells in a rat asthma model.^[19]^ LP has also been shown to potently inhibit airway inflammation and hyperresponsiveness in a murine model of asthma by modulating the relationship between Th1/Th2 cytokine imbalance.^[20]^ Most recently, LP has been noted to suppress the increased inflammatory cytokines in lung phagocytic cells or epithelial cells caused by fine dust in a dose-dependent manner.^[5,21]^

The proposed study will be the first at this stage to be conducted to determine the appropriate dosage and duration of LP administration. Although our sample size will be small and biases may result, this study will provide valuable insights into the underlying mechanisms of the anti-inflammatory effects and improvement of respiratory function caused by LP extract and will lay the groundwork for further studies.

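### Laboratory and biomarker outcomes: within-group and between-group tests are merged, and the only stated interval and purpose concern change from baseline, not LP against placebo

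*Protocol article*

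**What the plan says.** The sentence at issue is in the last paragraph of section 2.9 (Statistical analysis) of the protocol article. It begins "Continuous data such as comparisons between groups, individual laboratory test results, and biomarkers will be analyzed using", names paired t-tests or t-tests, and continues "with 95% confidence intervals within the group to determine if there are any changes compared to the baseline". If normality fails, the fallback again offers one test of each kind: "Wilcoxon signed rank test or Wilcoxon rank sum test) will be performed".

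That paragraph opens on safety: "The safety assessment calculates the rate of adverse events". Section 2.7 (Outcome measures), however, lists the biomarkers as secondary efficacy outcomes. Among them are seven immune factors, measured "to analyze allergic inflammation in the bronchi", and three antioxidant markers. The Discussion expects that "this study will provide valuable insights into the underlying mechanisms of the anti-inflammatory effects".

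The primary outcome is handled differently in the same section. For change in BCSS "between the 2 groups, the Mann–Whitney-Wilcoxon rank sum test will be performed", with a Hodges-Lehmann estimate of the treatment difference and a 95% nonparametric interval.

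**The concern.** A paired test in the LP arm asks whether values moved over four weeks. It cannot separate LP from whatever else moves values in both arms, such as symptoms that settle without treatment. Nor is it a test of LP against placebo to find a significant change on LP and none on placebo, because two p-values on either side of 0.05 do not measure the difference between the arms.

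The wording leaves that route open. Within-group and between-group tests are alternatives, no rule says which decides, and the stated purpose and interval point to the within-group one. No between-group estimate or interval is specified for these outcomes. At stake are the statements about anti-inflammatory mechanism, which depend on these variables. If the choice of test is settled only after unblinding, it can also be influenced by the results.

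**Working it through.** **Inputs from the article**
- Section 2.4: 10 per group, 5% dropout, 22 participants in total.
- Section 2.1: allocation 1:1.
- Section 2.9: 5% level. Sidedness is not stated, so two-sided is assumed.

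**The plan's own figure.** 10 / (1 − 0.05) = 10.53, rounded up to 11 per group, and 2 × 11 = 22. The stated total reproduces. The 10 per group comes from a cited pilot rule and is taken as given.

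**Assumption.** The article gives no SD and no expected change for any biomarker. Let d be the mean change divided by the SD of change, equal in both arms, so that LP has no effect. The range 0.3 to 1.0 is used, with changes normal and the arms independent.

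**Formulae, n = 11 per arm.** The paired t-test has 10 degrees of freedom, critical value 2.228 and noncentrality d√11.
- u = P(t > 2.228), the chance of a significant improvement in one arm.
- p = P(|t| > 2.228), the chance of significance in either direction.
- Chance that LP shows a significant improvement and placebo is not significant: u(1 − p).

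For d = 0.6 the noncentrality is 0.6 × 3.317 = 1.990. This gives u = 0.436 and p = 0.436 to three places, and 0.436 × 0.564 = 0.246.

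| d (same in both arms) | LP arm shows significant improvement | LP significant, placebo not |
|---|---|---|
| 0.3 | 14.5% | 12.4% |
| 0.5 | 32.3% | 21.9% |
| 0.6 | 43.6% | 24.6% |
| 0.8 | 66.8% | 22.2% |
| 1.0 | 84.8% | 12.9% |

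If one participant per arm is lost (n = 10), the LP-arm figures are 13% at d = 0.3, 29% at 0.5, 62% at 0.8 and 80% at 1.0. The LP-only figures are 12%, 21%, 24% and 16%.

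**Comparator.** A two-sample t-test on change is unaffected by a change that both arms share. In 100,000 simulated trials with 10 per arm it rejected 4.9 to 5.0% of the time for d = 0, 0.5 and 0.8. About half of that 5% two-sided error, 2.5%, favours LP. That is the closest comparison for both columns of the table, since each counts only results in LP's favour.

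**The case against.** The strongest reply is that the sentence does contain a between-group analysis. It lists comparisons between groups, it names t-tests beside paired t-tests, and the fallback includes the rank sum test, which compares two samples. On that reading it is a compressed description of the usual pairs: paired t or signed rank within arms, t or rank sum between them. This stands. A reader might infer that within-group testing is the only analysis planned for biomarkers, or that the plan will declare a within-group improvement to be an LP effect. The article supports neither, since between-group tests are named and no rule of that kind appears.

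A second reply is that the paragraph concerns safety, where change from baseline is routinely reported. This limits the point but does not remove it. The sentence names biomarkers, and section 2.7 makes them efficacy outcomes. The earlier sentence in section 2.9 on t-tests or rank sum tests for continuous data follows directly on demographic and clinical-history data, so it does not clearly cover them.

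A third reply is that the size depends on the assumed shared change. That is correct. By the same formulae at 11 per arm, LP-only significance falls to 4.6% at d = 0.1 and 7.9% at d = 0.2. Entry selects on symptoms, not on cytokines, IgE or antioxidants, so regression to the mean is a weaker argument for the biomarkers than for the symptom scores. What does not depend on the assumption is that the within-group test answers a different question.

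**Conclusion.** The point holds as a defect of specification. Section 2.9 merges two kinds of test, attaches the only interval and purpose to change within an arm, and does not say which result supports a statement about LP.

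If the within-group route were taken with no LP effect, each variable would show a significant improvement in the LP arm with probability 15 to 85%, and significance on LP alone with probability 12 to 25%. A between-group test holds 5% two-sided. These figures rest on 11 per arm, normally distributed changes and a shared change of 0.3 to 1.0 SD, which is assumed.

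The primary BCSS conclusion is not touched. A reader might also take the normality-driven choice of test or the number of secondary outcomes as adding to the problem. Neither is part of this point: the choice of scale is commonly left to an analysis plan, and section 2.4 already describes a pilot meant to explore the primary and secondary outcomes. For exploratory outcomes in a trial of 22 people this is a should-fix.

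**What to change.** Split the sentence in section 2.9 into two.

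1. For the continuous secondary outcomes, including the biomarkers, base any conclusion about LP on the between-group difference at Visit 2 adjusted for baseline (ANCOVA), with a 95% confidence interval for that difference. Where ANCOVA is not suitable, use a between-group rank-based comparison of change with its interval, as already planned for BCSS.
2. Report change from baseline within each arm descriptively, without p-values.

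Make the change before unblinding. It needs no further participants, visits or measurements, because these outcomes are already measured at both visits. The cost is some rewording, a little programming and the loss of within-group p-values.

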## Introduction

1

Respiratory disease has emerged as a global issue due to COVID-19, which has been prevalent since the end of 2019. In Korea, even before the onset of the COVID-19 pandemic, people were wary of respiratory diseases caused by fine dust. Among air pollutants, fine dust has recently been recognized as the most serious threat to human health.^[1]^ Fine dust affects the respiratory system in particular, as the small size of the particles allows for deposition in the lower bronchial tubes and parenchyma of the lungs, resulting in decreased lung function and increased respiratory symptoms.^[2]^

Bronchial inflammation resulting from fine dust exposure is the most common respiratory disease.^[3]^ The main respiratory symptoms are cough, sputum, shortness of breath, wheezing, and chest discomfort.^[4]^

Accordingly, a need for effective health functional food and medicine products and complementary medicine for respiratory diseases has emerged, and there has been increased interest in and development of products. The monocotyle flowering plant *Liriope platyphylla* (LP) is known to have antioxidant and anti-inflammatory effects^[5,6]^ and immunomodulatory abilities^[7]^ and has been widely used for lung and respiratory diseases. In particular, it is effective for treating bronchitis, pharyngitis, and asthma accompanied by dry cough.^[8,9]^

In this study, LP will be used as a raw material to derive medicine from a natural herbal supplement. The effects of LP on respiratory function, improvement of symptom, and the alleviation of inflammation will be tested.

The following protocol has been designed to verify the safety and efficacy of LP in treating respiratory system symptoms using a single-center, randomized, controlled, and double-blind clinical trial.

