### Study design

2.1

We designed a double-blind, single-center, randomized clinical trial to investigate the efficacy of LP in improving respiratory function. A total of 22 participants with respiratory symptoms (cough, sputum) will be recruited from outpatients at the Daejeon University Cheonan Korean Medicine Hospital (DUCKMH) through advertisements posted on bulletin boards at hospitals. Recruitment commenced in July 2021, and the trial is expected to end in December 2021. All participants will receive a full written explanation of the study protocol and an informed consent form.

Pulmonary function tests will be performed for those with respiratory symptoms, including cough or sputum, based on history or questionnaires. Additionally, blood tests for liver function, inflammation-related cells, and complete blood count will be performed.

A total of 22 participants who meet the eligibility criteria for this study will be randomly assigned in a 1:1 ratio to the treatment group (1000 mg LP) or control group (placebo). The intervention will begin within 2 weeks of the screening visit.

Based on the study group they are randomized into, the participants will be administered either 1000 mg LP or placebo for 4 weeks. The total duration of the clinical trial will be 4 to 6 weeks, and the efficacy and safety will be assessed at the second visit. A flowchart of the study is shown in Figure 1 and Table 1.

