### Randomization and blinding procedures

2.5

Randomization will be performed using the block randomization method in the experimental and control groups at a ratio of 1:1. The size of the block will be set randomly by a statistician. Subjects who meet all the registration criteria will be randomly assigned a randomization identification code (e.g., DLB-R-001, DLB-R-002, …, DLB-R-022) in the order generated by a computer-randomized program. The randomization number will be given to each participant and will indicate whether 1000 mg LP or placebo is to be given. As this pilot study was designed to be double-blinded, the participants, researchers, and assessors collecting the data will be blinded to the group allocation. Information on the intervention assignment will be stored in the statistical department. The randomization code will be placed in an opaque envelope and stored in the hospital. With the exception of disclosure of an individual patient's status in the case of a serious adverse event, randomization and blinding will not be disclosed to researchers until the end of the trial.

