### Safety

2.11

The occurrence of side effects will be assessed at each visit. Subjects will be monitored for undesirable and unintended symptoms, signs, and diseases. All adverse events will be classified and evaluated as mild, moderate, or severe. If a serious adverse event occurs, it will be reported to the IRB within 24 hours of identification and the participant will be required to withdraw. The number and ratio of participants who experience adverse events will be recorded.

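### Adverse events are compared only by chi-square and Fisher tests, with no governing rule and no interval; at 11 per group this says almost nothing about safety

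*Protocol article*

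**What the plan says.** The Introduction gives safety as one of the two aims: "The following protocol has been designed to verify the safety and efficacy of LP". The Safety section (2.11) grades events as mild, moderate or severe and adds: "The number and ratio of participants who experience adverse events will be recorded".

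The safety paragraph of Statistical analysis (2.9) opens with "The safety assessment calculates the rate of adverse events". It gives continuous laboratory results paired or unpaired t-tests with within-group 95% intervals, and Wilcoxon tests as the fallback. Categorical data get frequencies and ratios, followed by: "The differences between groups will be analyzed using the chi-square test and Fisher's exact test".

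Three things stand out in 2.9:

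- Baseline categorical data get chi-square *or* Fisher. The safety sentence joins the two tests with *and*, and does not say which one decides.
- The BCSS difference gets a Hodges-Lehmann estimate with a 95% interval, and laboratory changes get 95% intervals. Adverse-event rates and their difference get none.
- The 5% level is stated, but not whether tests are one- or two-sided.

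**The concern.** A significance test answers a useful safety question only if it has a fair chance of detecting an excess that matters. With 11 people per group that chance is small, so a non-significant result is the likely outcome whether or not LP causes more events. A reader would be left with a p-value and no statement of how large an excess the data still allow.

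Naming two tests adds a second problem. At counts this small they can fall on opposite sides of 5% for the same table. The article gives no rule for that case, so the choice could be made after the data are seen.

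Both problems bear on a stated aim of the trial, and on its use as groundwork for later studies.

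**Working it through.** **Inputs**

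- Group size. Study design states: "A total of 22 participants who meet the eligibility criteria for this study will be randomly assigned in a 1:1 ratio". That gives 22/2 = 11 per arm. It agrees with Sample size calculation: 10 per group with 5% dropout is 10/0.95 = 10.5, rounded up to 11, or 22 in total.
- Level: 5%. Two-sided is my assumption.
- True adverse-event rates: the article gives none. I assume 5% or 10% on placebo and 30% or 40% on LP, for illustration only.

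The article states no power or detectable difference for adverse events, so there is no safety figure of its own to reproduce.

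**Step 1: where Fisher reaches 5% with no placebo events.** With equal arms the two-sided p-value for *a* versus 0 is 2 × C(11,a)/C(22,a).

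- 4 v 0: 2 × 330/7315 = 0.090
- 5 v 0: 2 × 462/26334 = 0.035

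Five of 11 are therefore needed. At 10 per group the requirement is the same: 4 v 0 gives 0.087 and 5 v 0 gives 0.033.

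**Step 2: the other named test at 4 v 0.**

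- Uncorrected: 22 × (4×11 − 0×7)² / (11×11×4×18) = 4.89, p = 0.027
- Yates-corrected: 22 × (44 − 11)² / (11×11×4×18) = 2.75, p = 0.097

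The expected event count per arm is 11 × 4/22 = 2, below the usual limit of 5, so the chi-square approximation is poor here.

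**Step 3: power, by enumerating every 11 v 11 table with binomial weights.**

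| Assumed rates, placebo v LP | Fisher power | Uncorrected chi-square power | The two disagree |
|---|---|---|---|
| 5% v 30% | 12.7% | 27.3% | 14.5% |
| 10% v 30% | 7.5% | 17.0% | 9.5% |
| 10% v 40% | 19.1% | 33.9% | 14.7% |
| 5% v 40% | 30.1% | 49.0% | 18.9% |

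With the Yates correction, the disagreement with Fisher is 0% in all four rows. With 10 per group, Fisher's power falls to between 5.7% and 23.8%.

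**Step 4: what intervals would show.**

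- 0/11: exact two-sided 95% upper limit 1 − 0.025^(1/11) = 28.5%. For 0/10 it is 30.8%.
- 4/11: exact 95% interval 10.9% to 69.2%.
- 4/11 − 0/11 = 36.4 points: Newcombe 95% interval 2.9 to 64.6 points.

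**The case against.** Several objections stand and limit the point.

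- A reader might infer that these tests are the only safety inference in the plan. They are not: laboratory results have tests and within-group intervals. The point concerns adverse events alone.
- A reader might infer that 4 v 0 would simply be reported as no difference. That is true of two-sided Fisher and of Yates, but not of uncorrected chi-square. One-sided Fisher gives 0.045.
- A reader might infer that non-significance will be taken as proof of safety. No section says so, and the rates are reported too, so 4 of 11 against 0 of 11 would be visible. The misreading is a risk, not a stated rule.
- The 10–19% disagreement depends on the uncorrected chi-square, which the article neither specifies nor excludes.
- Low power follows from a pilot of 22, and no analysis removes it. The Discussion admits that the sample is small.
- A Newcombe interval reported beside Fisher would recreate the conflict. It excludes zero at 4 v 0, and over the four scenarios it disagrees with Fisher in the same 10–19% of trials. The remedy must therefore avoid pairing them.

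It can also be said that a condensed article may leave intervals to a fuller plan. That would be enough if the complaint were only an omission. But the article does state its adverse-event comparison, and that comparison is a poor choice at this size.

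**Conclusion.** The concern holds for adverse events. The stated comparison consists of rates plus p-values from two tests with no governing rule. At 11 per group, two-sided Fisher needs 5 v 0 and has 8–30% power in the assumed scenarios. At 4 v 0 the result is 0.090, 0.027 or 0.097 depending on the version read. A trial with no events on LP could still not exclude a true rate of up to 28.5%.

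The power and disagreement figures rest on assumed rates and two-sided testing; the disagreement also needs the uncorrected chi-square. The Fisher threshold and the 28.5% limit do not depend on assumed rates. The documents do not support the stronger reading that the plan hides harm or declares safety from a non-significant test. What they support is that the chosen analysis is nearly uninformative for a stated aim, and that a better one is available from the same data.

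**What to change.** In Statistical analysis (2.9), make estimation the adverse-event analysis. Suggested wording: *The number and percentage of participants with at least one adverse event will be given per group with exact (Clopper-Pearson) 95% confidence intervals, and the risk difference (LP minus placebo) with a 95% Newcombe interval. Safety will be described from the upper limits of these intervals. A non-significant result will not be taken as evidence of safety.*

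Another interval for the difference would also serve, provided that one is named in advance. Drop the adverse-event significance tests. If a p-value is kept, pre-name a single test consistent with the chosen interval; Fisher beside a Newcombe interval would not meet this.

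The change needs no new data and does not affect conduct. It costs a few extra lines of output and a less favourable safety statement: with no events on LP, the report would have to say that a true rate of up to 28.5% is not excluded.
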